#### Secondary endpoints

The following secondary endpoints will be recorded:
Static lung compliance (ml/cmH_2_O) (measured at least once daily at 8:00 a.m. during the first 7 days)Duration of mechanical ventilation (h) from ICU admission to first extubation success (> 48 h without reintubation)Length of ICU stay (h)Length of stay in the hospital (days)Incidence of multi-organ failure (a SOFA score of 3 or more in at least two organ systems [49]), assessed daily during the first 7 daysIncidence of VAP according to both the American Thoracic Society (ATS) [50] and the Center for Disease Control and Prevention (CDC) [51] definitions, assessed daily during the first 7 daysMortality on day 30

The effects of dornase alfa and normal saline will be assessed according to the plasma concentrations of DAMPs (mitochondrial DNA, HMGB-1, HSP70, sRAGE) and NETs (Strasbourg centre only) divided into quartiles at day 0, day 3 and day 5. It is anticipated that trauma patients with the highest blood concentrations of either DAMPs or NETs will develop the most severe complications (including hypoxaemia and ARDS). The time course of DAMP and NET blood concentrations will also be analysed according to treatment group to unveil a potential quicker decrease in patients randomized in the dornase alfa group.

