The aim of this study is to show that the frequency of moderate-to-severe hypoxaemia is lower in the dornase alpha group than in the placebo group. The main variable is then dichotomous “moderate-to-severe hypoxaemia yes/no”, modelled in a logistic mixed regression. We will assume that this variable is Bernoulli distributed with parameter π. The logit of this parameter (linear predictor) is additively written as:
$$ \mathrm{logit}\left({\pi}_i\right)={\alpha}_0+{\alpha}_1I\left({g}_i=1\right)+{\beta}_i, $$

where:
*α*_0_ is a grand mean, with mean 0 normal prior (the variance in this normal is 6, corresponding to a low informative prior)*I*(*g*_*i*_ = 1) is a dummy covariate coded for the group of subject *i* (1 for the dornase alpha group and 0 for the placebo group) — the prior on the parameter of this covariate is the same normal as that for the grand mean*β*_*i*_ is a (random) subject effect, on which is assumed a normal prior with mean 0 and low variance (e.g. 10)

Because the linear predictor is on the logit scale, the probability for moderate-to-severe hypoxaemia will be obtained by monitoring the back-transformation of the logit.

This regression model without covariates except group will be completed for taking into account potential confounding variables. In the model, the entire set of these variables will be added and, secondly, selected using stochastic search variable selection (SSVS) [53]. In such a model, the prior distribution on each parameter is a mixture of two mean 0 normal distributions, one with low variance and the other with high variance: if the posterior weight on this second normal is strongly around 0, then the prior on the parameter is essentially driven by a normal distribution whose mean is centred on 0; this is the clue for a “non-significant” parameter.

The secondary analyses will be conducted as the main analysis with a regressive model, testing the difference of a parameter between the two groups. Only the likelihood model will be changed to take into account the type of variable studied: γ distribution for continuous variables such as length of stay and duration of ventilation. Dichotomous variables such as 30-day mortality will be studied with logistic regression.

No statistical procedure for replacing missing values will be used. All variables and subjects will be considered in the descriptive analyses, but, for inference, 20% missing data or more will result in rejection of the variable or individual.

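### The one rule given for secondary analyses has no day, group-by-day or day-0 term, so read literally it does not isolate the quicker DAMP/NET decrease that the secondary endpoints section looks for (low severity)

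*Protocol article*

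**What the plan says.** Under Statistical methods {20a}, the primary outcome is modelled with a linear predictor made of an intercept, a group indicator and a random subject effect. The indicator "is a dummy covariate coded for the group of subject" *i*, and every term is indexed by subject only. The article adds: "This regression model without covariates except group will be completed for taking into account potential confounding variables", with selection by SSVS. It then sets the rule for the rest: "The secondary analyses will be conducted as the main analysis with a regressive model, testing the difference of a parameter between the two groups", followed by "Only the likelihood model will be changed to take into account the type of variable studied". The examples given are a gamma distribution for length of stay and ventilation duration, and logistic regression for 30-day mortality.

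The Secondary endpoints section, in a paragraph after the endpoint list, says: "The time course of DAMP and NET blood concentrations will also be analysed according to treatment group", with the purpose "to unveil a potential quicker decrease in patients randomized in the dornase alfa group". The Ancillary mechanistic study section sets the blood samples at days 0, 3 and 5 and measures NETs at the Strasbourg centre only.

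Elsewhere in the statistical section, time appears only in the descriptive step, where repeated variables are summarised overall and at each time point.

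**The concern.** A quicker decrease is a between-group difference in change from a starting value. To estimate it, the model needs a group-by-day term, a change from day 0 as outcome, or the day-0 value as a covariate. The article names none of these, and the word restricting changes to the likelihood leaves no evident room for them. The two sections therefore do not fit together as written.

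What is at stake is interpretation and precision in the biomarker work. If the three days are pooled under the stated predictor, the group coefficient is a difference in average level. It includes day 0, when little or no treatment effect can be present, and it leaves unused a baseline value that is already being collected.

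**Working it through.** The article gives no SD, correlation, effect size or target power for the markers, so there is no figure to reproduce. The first step is algebra; the rest is illustration under stated assumptions.

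**Inputs**
- Sampling days 0, 3 and 5 (Ancillary mechanistic study).
- 200 patients per arm (Sample size {14}, before the allowance for loss).
- Assumed: SD of 1 on each day, the same within-patient correlation *r* for every pair of days, *r* = 0.3, 0.5 or 0.7, complete data, two-sided 5% normal test. The plan is Bayesian; power serves here only as a measure of precision.

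**1. What the pooled group coefficient measures.** With balanced data it is the difference between arms in patient means. The mean sampling day is (0 + 3 + 5)/3 = 8/3, so under linear change

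coefficient = day-0 difference + (8/3) × slope difference.

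It can be zero when slopes differ and non-zero when declines are parallel.

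**2. Dilution of a later effect.** Suppose the true difference is 0 on day 0 and 0.3 SD on days 3 and 5.
- Pooled: effect (0 + 0.3 + 0.3)/3 = 0.2 SD; variance per patient (1 + 2*r*)/3.
- Mean of days 3 and 5 adjusted for day 0: effect 0.3 SD; residual variance (1 + *r*)/2 − *r*².
- In both cases z = effect / √(2 × variance / 200).

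| *r* | Pooled variance | z | Power | Adjusted variance | z | Power |
|---|---|---|---|---|---|---|
| 0.3 | 0.533 | 2.74 | 0.78 | 0.56 | 4.01 | 0.98 |
| 0.5 | 0.667 | 2.45 | 0.69 | 0.50 | 4.24 | 0.99 |
| 0.7 | 0.800 | 2.24 | 0.61 | 0.36 | 5.00 | 0.999 |

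**3. Sensitivity to the shape of the effect.** Take instead a slope difference of 0.05 SD per day from equal baselines, and compare the pooled coefficient (0.05 × 8/3 = 0.133 SD) with a group-by-day slope. The slope has variance (1 − *r*)/12.67, where 12.67 is the sum of squared deviations of the days from 8/3.

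| *r* | Pooled z | Power | Slope z | Power | Ratio of z, slope/pooled | Ratio of z, adjusted/pooled (step 2) |
|---|---|---|---|---|---|---|
| 0.3 | 1.83 | 0.45 | 2.13 | 0.57 | 1.16 | 1.46 |
| 0.5 | 1.63 | 0.37 | 2.52 | 0.71 | 1.54 | 1.73 |
| 0.7 | 1.49 | 0.32 | 3.25 | 0.90 | 2.18 | 2.24 |

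In signal-to-noise terms, the slope contrast gains less than day-0 adjustment at every *r*. At *r* = 0.3 it adds only 12 points of power.

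**4. Chance imbalance on day 0.** The NET analysis is the smallest. If enrolment follows the listed centre volumes (total 1170, Strasbourg 150), that centre contributes about 500 × 150/1170 = 64 patients, or 32 per arm. A chance day-0 difference then has a 95% range of ±1.96 × √(2/32) = ±0.49 SD, and a share (1 + 2*r*)/3 of it passes into the pooled coefficient: 0.49 × 0.533 = 0.26 SD at *r* = 0.3 and 0.49 × 0.80 = 0.39 SD at *r* = 0.7. The 95% half-width of the pooled coefficient itself is 1.96 × √((2/32) × (1 + 2*r*)/3) = 0.36 SD at *r* = 0.3 and 0.44 SD at *r* = 0.7. The carried-over imbalance is the smaller at each matching *r*, because it is already part of the sampling variance.

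**The case against.** The strongest defence is that the secondary-analysis rule may not govern the markers. The work is headed as an ancillary mechanistic study, no marker appears among the secondary objectives, and the examples given with the rule have one value per patient. A condensed article may leave an ancillary model to a fuller document. This lowers the severity. It does not remove the point: the time-course aim stands under the Secondary endpoints heading, {20a} covers primary and secondary outcomes, and its rule is the only inferential one given for them.

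Second, pooling the three days is only one reading. The predictor is fixed but the marker outcome is not. The same model applied to change from day 0, or with the day-0 value among the added covariates, would answer the question. That is correct, but the article states neither. A raw change score for a falling marker is negative, so it would not suit the gamma likelihood, the one named for continuous outcomes in that paragraph.

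Three stronger readings are tempting, and the document does not support them.
- *The plan cannot show a difference in decline.* Randomised arms have equal expected baselines, so a later level difference carries information on decline. The stated coefficient simply does not isolate it.
- *A chance day-0 imbalance would be taken for a drug effect.* Step 4 shows that the unconditional false-positive rate is not inflated.
- *This is the only test of the mechanism.* The article also plans to assess treatment effects by quartile of DAMP and NET concentration, and its time-course wording is exploratory.

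**Conclusion.** The point holds in limited form. Read literally, {20a} and the Secondary endpoints section do not match: the first states a predictor without day, group-by-day or day-0 value, and the second asks about decline. Under pooling, the cost is blurred meaning and lost precision, not false-positive error. For a 0.3 SD effect confined to days 3 and 5, with 200 per arm and *r* from 0.3 to 0.7, power is about 61 to 78% pooled, against 98% or more with day-0 adjustment. These figures depend on the assumed effect shape, equal SDs and complete samples, and the numbers will be much smaller for NETs. The primary endpoint, sample size and main conclusion are untouched. Severity is low.

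**What to change.** Add one exception to the secondary-analysis rule in {20a} for the marker time course:
- Model log concentration on days 3 and 5 with day, group, group-by-day, the patient's day-0 log concentration and a patient effect.
- Report the baseline-adjusted group difference at day 3 and at day 5. Given the day-0 value, the adjusted difference in level and in change from day 0 are the same number, so this directly expresses a quicker decrease.
- State that the day-0 sample is drawn before the first aerosol. Table 1 puts both on day 0 without giving their order, and the value is a baseline only if the sample comes first.

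The cost is a few lines of analysis-plan wording and one line in the sampling instructions. The samples are already planned, and no further patients or data are needed.

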#### Interim analyses {21b}

An interim analysis will be performed after inclusion of the first 250 patients. These preliminary data will be available to the data safety and monitoring board (see later for details), which will have the ability to stop the trial for either futility or harm.

#### Methods for additional analyses (e.g. subgroup analyses) {20b}

Analyses will be performed in intention to treat. To verify the impact of possible deviations from the protocol, these analyses will be supplemented by an analysis per protocol. Subgroup analyses will be conducted according to the Glasgow Coma Scale on site (score either ≤ 8 or > 9).

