### Trial design {8}

This will be an investigator-initiated, institution-led, multicentre, double-blinded, placebo-controlled, parallel-group, superiority, randomized trial in ventilated, trauma ICU patients.

Randomization will be carried out through a secure web-based randomization system, stratified by the centre and the presence of severe traumatic brain injury (Glasgow Coma Score < 9 on scene).

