### Participant timeline {13}

The total duration of participation in the study will be 30 days. The forecast study duration is 36 months from first to last patient recruitment (Table 1).

**Table 1 Tab1:** Template of recommended content for the schedule of enrolment, interventions and assessments

	Visit				
	Information	Enrolment	Allocation, visit 0	Post-allocation, visits 1–7	Close-out
Timepoint	Day 0	Day 0	Day 0	Days 1–7	Day 30
Location	Hospital	Hospital	Hospital	Hospital	Hospital
Next of kin information	X*	X*	X		
Signed informed consent		X*			
Plasma **β**HCG assay		X(*)			
Eligibility criteria check	X*	X*	X*		
Randomization			X*		
Study drug administration			X*^d^	X*^d^	
Clinical examination^a^		X	X	X	
Diagnostic tests^b^		X	X	X	
Blood assay^c^			X*	X*	
Adverse effect recording		X*	X*	X*	X*
Concomitant medications		X	X	X	X

*βHCG* beta human chorionic gonadotropin, *X* diagnostic test performed on a daily basis according to the standard of care in participating centres, *X** diagnostic tests performed for the purpose of the TRAUMADORNASE study

^a^Clinical examination includes physical examination (auscultation of the chest, central body temperature, positive end-expiratory pressure and inspired oxygen fraction levels) and recording of Utstein criteria [49]

^b^Diagnostic tests include arterial blood gases, chest X-ray, leukocyte and platelet counts, creatinine, blood urea nitrogen, bilirubin and quantitative lung bacteriologic samplings (bronchoalveolar lavage fluid or protected specimen brush) in the case of suspected lung infection

^c^Blood withdrawal: 6 ml of blood on day 0, day 3 and day 5

^d^Study treatment will be given on day 0 and day 1

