### Assignment of interventions: allocation

#### Sequence generation {16a}

Randomization will be conducted over a dedicated, password-protected, SSL-encrypted website (CleanWeb; Telemedicine Technologies S.A.S.) to allow immediate and concealed allocation. Allocation will also be stratified by centre and the presence of severe traumatic brain injury (Glasgow Coma Score < 9 on scene).

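### The Glasgow subgroup rule leaves a score of 9 in neither group, and the biomarker quartiles at days 3 and 5 would group patients by a variable measured after treatment

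*Protocol article*

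**What the plan says.** **Glasgow subgroup.** Protocol article, section {20b}: "Subgroup analyses will be conducted according to the Glasgow Coma Scale on site (score either" 8 or less, or above 9). It is the only subgroup analysis named in that section. The randomisation factor appears twice. Trial design {8} has allocation "stratified by the centre and the presence of severe traumatic brain injury (Glasgow Coma Score < 9 on scene"), and Sequence generation {16a} repeats it: "Allocation will also be stratified by centre and the presence of severe traumatic brain injury (Glasgow Coma Score < 9 on scene").

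**Biomarker quartiles.** The secondary endpoints section says: "The effects of dornase alfa and normal saline will be assessed according to the plasma concentrations of DAMPs" (and of NETs, at one centre only), "divided into quartiles at day 0, day 3 and day 5". The same paragraph anticipates that patients with the highest concentrations will have the worst complications, hypoxaemia and ARDS included. It then plans a separate comparison of the time course by arm, looking for a faster fall under dornase alfa. On timing, the footnote to the schedule in Participant timeline {13} reads: "Study treatment will be given on day 0 and day 1".

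**The concern.** A subgroup rule should place every randomised patient in exactly one group. This one does not, and whoever runs the analysis would have to decide where patients scoring 9 go. If that is settled after unblinding, the choice is open to question.

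The quartile plan matters more. A comparison of arms is protected by randomisation only within groups fixed before treatment. Day-3 and day-5 concentrations come after both doses. If the drug lowers a marker that reflects severity, a treated patient in a given day-3 quartile will tend to have been sicker at the start than a control patient in that quartile. The arms then differ within quartiles even when the drug does nothing to oxygenation. The primary endpoint also covers the first 7 ICU days, so some events can precede the sample that classifies the patient. At stake is how the mechanistic results are interpreted; the primary result is not affected.

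**Working it through.** **1. Glasgow rule.** The scale is taken as integers 3 to 15 (the standard scale; the article does not state it).

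| Definition | Lower group | Upper group | Left out |
|---|---|---|---|
| Subgroups, {20b} | 3–8 | 10–15 | 9 |
| Strata, {8} and {16a} | 3–8 | 9–15 | none |

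On integers, 8 or less is the same as below 9, so the lower subgroup is exactly the severe stratum. The upper subgroup differs from its stratum only by the score of 9. The gap and the mismatch are one defect.

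The article gives no Glasgow distribution. Patients left out = 500 × share scoring 9:
- 1%: 500 × 0.01 = 5
- 3%: 15
- 5%: 25
- 10%: 50

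**2. Timing.** Doses fall on days 0 and 1; samples on days 0, 3 and 5. The day-3 and day-5 samples therefore follow both doses. For day 0, the schedule puts blood sampling and drug administration at the same visit without giving their order.

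**3. Size of the bias.** The article gives no figure, so this is a simulation on assumed values, with 2,000,000 patients allocated 1:1 and no effect of treatment on outcome.
- Day-0 marker: b ~ N(0, 1).
- Day-3 marker: m = 0.7·b + √(1 − 0.49)·e − d·t, with e ~ N(0, 1), t = 1 for dornase alfa, and d the fall in SD units.
- Outcome: logit P(hypoxaemia) = −0.25 + 1.0·b, which gives a control rate of about 45%, the article's planning figure.

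Risk difference, drug minus placebo, in percentage points by day-3 quartile (lowest to highest), with the share of each quartile that is treated:

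| d | Q1 | Q2 | Q3 | Q4 | Share treated, Q1 to Q4 |
|---|---|---|---|---|---|
| 0 | −0.2 | −0.2 | 0.0 | 0.0 | 50, 50, 50, 50% |
| 0.25 | +2.5 | +3.7 | +3.6 | +2.9 | 58, 52, 48, 42% |
| 0.50 | +4.8 | +7.4 | +7.5 | +5.7 | 66, 54, 46, 35% |
| 0.75 | +7.2 | +10.6 | +11.1 | +8.2 | 73, 56, 43, 27% |

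The true difference is zero in every cell. Day-0 quartiles stay within ±0.2 points and 50:50 by arm at every value of d. When the drug does not move the marker (d = 0), the day-3 quartiles are unbiased too.

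For scale, the trial's target is 45% − 30% = 15 points. At d = 0.5 the false difference runs from 4.8/15 = 32% to 7.5/15 = 50% of that target, in the opposite direction.

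**The case against.** **The Glasgow point is small.** It is probably a slip for above 8, or for 9 or more. The score is recorded before randomisation, so leaving out patients who score 9 costs precision but does not bias the comparison, and the primary intention-to-treat analysis keeps them. All of that stands. A reader might infer that the subgroup analysis abandons the randomisation strata altogether; it does not, because the lower group is its stratum exactly.

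**The quartile sentence is loosely worded.** It does not literally say that arms will be compared within day-3 or day-5 quartiles, and could be read as describing prognosis. It also concerns ancillary work whose details may sit elsewhere. But its subject is the effects of the two treatments, and the time course by arm is announced as a further analysis. The within-quartile comparison is the more natural reading.

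**The bias is not certain.** A reader might infer that a spurious effect must appear whenever the drug lowers the marker. The marker must also be related to outcome through severity. The protocol anticipates both conditions but establishes neither, and gives no size for any fall in plasma concentrations after an aerosol.

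**The trial is too small to show it.** With about 125 patients per quartile (62 per arm) and a rate near 0.425, the standard error of the arm difference is √(2 × 0.425 × 0.575 / 62) = 0.089, about 9 points. The simulated bias at shifts of 0.25 and 0.5 SD is below that in every quartile. This stands for a single quartile. But the bias has the same sign in all four, so averaging does not remove it. At 0.5 SD the mean is (4.8 + 7.4 + 7.5 + 5.7)/4 = 6.35 points, against a standard error of roughly √(2 × 0.425 × 0.575 / 250) = 0.044, about 4.4 points, over all 500 patients.

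**Conclusion.** Both parts hold, at different weights.

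The Glasgow rule contains a definite gap at score 9. It affects one secondary analysis, costs precision only, and involves an unknown number of patients (5 to 50 of 500 under an assumed 1% to 10%).

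The day-3 and day-5 quartile comparisons condition on a post-treatment variable. They would be biased if the protocol's own two expectations hold: that the markers predict outcome, and that the drug lowers them. The size, about 2.5 to 11 points for shifts of 0.25 to 0.75 SD, depends on the assumed shift, a correlation of 0.7 between days 0 and 3, and a log-odds slope of 1.0 per SD; none of these comes from the documents. A reader might infer a risk of a false claim of benefit. The likely direction is the reverse: the bias would make dornase alfa look worse, or hide a real benefit, within quartiles. The time-course comparison by arm and the primary analysis are not affected.

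**What to change.** 1. In section {20b}, define the subgroups as the randomisation strata: Glasgow score on scene of 8 or less v 9 or more. This is a one-character correction and needs no new data.
2. In the secondary endpoints section, restrict the assessment of treatment effect by biomarker quartile to the day-0 sample, and state that it must be drawn before the first dose. If the order varied in practice, limit the analysis to patients sampled before dosing. This costs nothing if sampling came first. If it did not, some or all of the day-0 analysis is lost, and the documents do not let the reader tell which.
3. Use day-3 and day-5 concentrations only as outcomes, in the time-course comparison by arm that is already planned. The day-3 and day-5 quartile comparisons are then dropped, or kept as description with no inference about treatment effect.

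Make these changes before unblinding.

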#### Methods in analysis to handle protocol non-adherence and any statistical methods to handle missing data {20c}

No statistical procedure for replacing missing values will be used. All variables and subjects will be considered in the descriptive analyses, but, for inference, 20% missing data or more will result in rejection of the variable or individual.

